### Data analysis

We require 130 participants to detect pre–post intervention change in the MLFHQ scores to achieve the minimal important difference^13^ ≥5 points. This calculation is based on a MLHFQ SD of 24 points, within patient pre–post correlation (r=0.72) and attrition rate of ≤10% as seen in our multicentre RCTs refs. There is no formal sample size calculation for the number of caregivers participating in this study.

#### Fidelity

Fidelity data will be analysed by CP. Fidelity checklist scores will be collated at facilitator, site and total sample levels. We will present descriptive statistics (means, ranges), using the same analytic approach as the original REACH-HF trial.^13^ In brief, the fidelity checklist uses an established 0–6 scale (Dreyfus scale of clinical skills acquisition^28^) to rate clinical skills, and is anchored such that a score of three or more represents adequate delivery quality for each item. Fidelity outcomes will be compared with the REACH-HF RCT,^13^ and analysed alongside self-rated fidelity scores. Overall findings will be integrated with the context and CR participant-related outcome data findings.

#### CR participant-related outcomes

The primary analyses for primary and secondary quantitative outcomes will based on a within-patient comparison in participants with complete outcome data at 4 months. We will examine the characteristics of any patients who withdraw, and conduct secondary analysis based on imputation of their missing outcome data. All within-patient outcome comparisons will be presented as mean difference with 95% CI. The outcome effect size seen in the Beacon Sites will be indirectly compared with the changes found in the REACH-HF trial.^13^ Statistical analysis will be conducted by RT using STATA V.15. Descriptive statistics will be presented in order to describe study population characteristics.

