### Sample and recruitment

The study will be conducted across Scottish NHS ‘Beacon Sites’. People with HF are eligible if they: are aged 18 years or over; have a confirmed diagnosis of systolic (reduced ejection fraction) HF within the past 5 years; have experienced no deterioration of HF symptoms in the preceding 2 weeks resulting in hospitalisation or alteration of HF medication; and are deemed suitable for CR by their local clinical team. We will exclude anyone who: has undertaken CR in the preceding 12 months; has medical contraindications to exercise testing or training; is in a long-term care establishment, or unwilling/unable to travel to research assessments or accommodate home visits; is unable to understand the study information or unable to complete the outcome questionnaires. Patients with a caregiver will also be invited to participate. Patients with no caregiver, or whose caregivers do not wish to participate, are still eligible take part in the study.

Sites will recruit people with HF, using their usual means of CR referral to introduce the study. This is likely to include a variety of pathways such as: people with HF referred for CR from acute or primary care; review of patients held on site HF databases; and approaching people with HF at outpatient appointments/home visits. Potential participants will be provided with invitation letters, information sheets, and reply slips for both them and their caregiver (if applicable), and those interested in participation will be asked to instigate contact with the research team by returning the reply slips. Figure 1 outlines the participation pathway for people with HF.

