### Measures/data collection

Patient and caregiver outcome data will be collected during an initial assessment appointment by a designated member of the Beacon Site team trained in data collection by the REACH-HF team, and via self-completion questionnaires (either postal or online, as per participants’ preference). Data will be collected at baseline—before commencing with the REACH-HF programme—and 4 months following baseline, which coincides with the end of intervention delivery period (see figure 1).

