#### CR participant-related outcomes

Data will be recorded in an electronic case report form (CRF), and participants will be offered the option of a paper self-completion questionnaire or a secure individual link sent by email to complete the questionnaire online. At the baseline appointment, after obtaining written consent, Beacon Site teams will collect medical history from the participants’ hospital and primary care records, including: comorbidities (number and severity scored with Charlson Comorbidity Index); New York Heart Association class; HF aetiology; concomitant HF medication and presence of implantable HF devices.

Participants will provide detailed sociodemographic data (age, gender, ethnicity, weight, employment status, education level, smoking status) at baseline. The following participant outcomes will be assessed: disease-specific HRQoL measured using the MLHFQ; generic quality of life (five-dimension EuroQol (EQ-5D-5L) scale); psychological well-being (Hospital Anxiety and Depression Scale (HADS)); patient-reported outcome measure for cardiac rehab; hospitalisations and primary care contacts (number, reason, duration); adverse events (eg, skeletomuscular injury); health literacy (Health Literacy Questionnaire); and, if possible, exercise capacity via an incremental shuttle walk test (if face-to-face assessment possible). Caregiver outcomes are: generic quality of life (EQ-5D-5L); psychological well-being (HADS); Family Caregiver Quality of Life Scale questionnaire; Caregiver Burden Questionnaire HF; Caregiver Contribution to Self-care of HF Index questionnaire. The same outcomes will be collected at the 4-month follow-up.

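### Read literally, hospitalisation and contact counts (and possibly adverse events) are analysed as a pre–post mean difference in 4-month completers, a rule that suits event outcomes poorly

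*Protocol article*

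**What the plan says.** Under Measures/data collection, the subsection on CR participant-related outcomes includes these items in the list of participant outcomes: "hospitalisations and primary care contacts (number, reason, duration); adverse events (eg, skeletomuscular injury". It closes with "The same outcomes will be collected at the 4-month follow-up". The Measures/data collection section places that follow-up at "4 months following baseline, which coincides with the end of intervention delivery period". It gives no period over which events before baseline are to be counted.

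Under Data analysis, the subsection of the same name sets one rule. "The primary analyses for primary and secondary quantitative outcomes" are to rest on a "within-patient comparison in participants with complete outcome data at 4 months". The presentation is fixed as well: "All within-patient outcome comparisons will be presented as mean difference with 95% CI". Event and safety outcomes have no rule of their own.

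The same paragraph offers some mitigation. The characteristics of patients who withdraw will be examined, and the team will "conduct secondary analysis based on imputation of their missing outcome data".

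Sample and recruitment bears on the baseline period. Patients must have had "no deterioration of HF symptoms in the preceding 2 weeks resulting in hospitalisation or alteration of HF medication", and referral from acute care is one of several recruitment routes.

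**The concern.** The rule suits a questionnaire score measured twice. It suits event outcomes poorly, for three reasons.

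- **Population.** A patient who dies or withdraws before 4 months has no within-patient change, so events that this patient had after baseline are not in the primary comparison. The Introduction itself describes heart failure as carrying a high risk of admission and poor survival.
- **Contrast.** A count of admissions before baseline depends on how far back one looks and on how patients came to be recruited. A change from that count is not a clean measure of the programme. An adverse event of the programme has no meaningful baseline value.
- **Measure.** A mean difference is a poor summary of sparse, skewed counts.

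At stake is how harm and admissions are reported. The study has no concurrent control group to expose a spurious fall in admissions. Such a fall would agree with the benefit on hospitalisation that the Introduction cites for cardiac rehabilitation. The Discussion says that the findings will inform wider roll-out.

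**Working it through.** **The plan's own figure.** The only sample size figure is 130, under Data analysis, for MLHFQ. SD of change = 24 × √(2 × (1 − 0.72)) = 17.96. With two-sided 5% and 85% power (both assumed, as neither is stated), n = ((1.960 + 1.036) × 17.96 / 5)² ≈ 116, and 116 / 0.90 ≈ 129. So 130 is reproduced closely. It says nothing about events, and the documents give no event rates. What follows is arithmetic on labelled assumptions.

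**1. Loss from a completers-only analysis**

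Inputs from the article: 140 patients (Study design) and attrition of 10%, the upper limit given under Data analysis, so 14 patients without follow-up.

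Assumed: a proportion p of 5% to 15% of completers hospitalised, and a risk in non-completers of R × p, with R from 1 to 4.

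- Proportion in all patients = 0.9p + 0.1Rp = p(0.9 + 0.1R)
- Understatement by the completer figure = 0.1p(R − 1)
- Share of hospitalised patients dropped = 0.1R / (0.9 + 0.1R)
- Number dropped = 14 × R × p

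| R | Share dropped | Understatement, p = 5% | p = 10% | p = 15% |
|---|---|---|---|---|
| 1 | 10% | 0 points | 0 | 0 |
| 2 | 18% | 0.5 | 1.0 | 1.5 |
| 3 | 25% | 1.0 | 2.0 | 3.0 |
| 4 | 31% | 1.5 | 3.0 | 4.5 |

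The number of hospitalised patients dropped runs from 14 × 1 × 0.05 = 0.7 to 14 × 4 × 0.15 = 8.4. With equal risk the proportion is unbiased, although a tenth of the hospitalised patients still go uncounted.

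**2. A before–after difference with no treatment effect**

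Assumed: a constant rate λ of 0.3 to 0.9 admissions per patient-year before and after baseline. With a look-back of W months against 4 months of follow-up, the mean difference is λ × (4 − W) / 12.

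- W = 3: +0.025 to +0.075 admissions per patient
- W = 4: 0
- W = 6: −0.05 to −0.15
- W = 12: −0.20 to −0.60

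The 2-week stability rule removes some admissions just before baseline. If it covered all admissions, which overstates its reach because it concerns only deterioration of heart failure, a matched 4-month look-back would give λ × 14 / 365.25 = +0.01 to +0.03. Acute-care referral works the other way by adding admissions before baseline. The documents give nothing from which to size that effect.

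**The case against.** The strongest case on the other side has four parts.

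- **The mitigation is in the same paragraph.** A reader might infer that the events of non-completers disappear from the study. The documents do not support that: withdrawals will be described, and their outcomes imputed in a secondary analysis. The loss is from the primary comparison. Even so, imputation estimates events that records could show, and it does not deal with deaths.
- **Adverse events may not be covered.** The rule governs quantitative outcomes, and a within-patient change in programme-related adverse events can hardly be computed. The authors may well have meant to report them otherwise, and no sentence restricts adverse event reporting to completers. This stands, so adverse events are included here only as a possible reading. Number and duration of admissions are plainly quantitative.
- **Events need not depend on a returned questionnaire.** The source of the hospitalisation data is not stated, completeness could be judged outcome by outcome, and site staff do enter data from medical records (Data management). An admission does not prevent a patient from completing a postal or online form. A reader might infer that non-completers are the patients with most events. That is plausible, but the article gives no rates by completion status, so the range above starts at equal risk.
- **The article is condensed.** The full analysis plan is not shown and may treat events separately. That would answer a complaint of silence. Here the published text states a general rule that takes in admission counts and makes no exception.

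A reader might also infer that the comparison is bound to show an artefactual fall in admissions. It is not. The direction depends on the unstated look-back and on the recruitment mix, and with a matched window at a constant rate the difference is zero or close to it.

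**Conclusion.** The concern holds in a limited form. As written, hospitalisation and primary care contact counts fall under a completers-only pre–post mean difference, and adverse events do too if they count as quantitative. For hospitalisations this is a stated rule that fits poorly.

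At 10% attrition, with 5–15% of completers hospitalised and 1 to 4 times that risk in non-completers, the primary analysis drops 10% to 31% of hospitalised patients and understates the proportion by 0 to 4.5 percentage points. With a look-back of 3 to 12 months, a constant rate of 0.3 to 0.9 per year and no treatment effect, the pre–post difference lies between −0.60 and +0.08 admissions per patient. All event rates, risk ratios and look-backs are assumptions.

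This should be corrected before analysis, but it does not undermine the study. The sample size rests on MLHFQ, and the Economic impact analysis lists staff time, supervision, training and consumables as the expected resource use, not admissions.

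**What to change.** Exempt event outcomes from the general rule in the Data analysis subsection on CR participant-related outcomes, and add a short paragraph to this effect:

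- Deaths, hospitalisations and adverse events are reported from baseline to 4 months in everyone who starts REACH-HF, whether or not 4-month questionnaire data exist.
- They are given as numbers of patients with an event and as rates over observed time. Use exact 95% CIs for proportions and, for rates, intervals that allow for repeat events within a patient.
- Where the 4-month questionnaire is missing, events come from medical records, as far as consent allows. The sponsor should confirm that consent covers this check.
- A pre–post change in admissions is not read as an effect. If one is shown, the look-back equals the follow-up in length and the result is labelled descriptive.

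The cost is a paragraph of text and a 4-month record check for those without follow-up data: about 10% of 140, or 14 patients. Site staff already enter data from medical records.

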Running parallel to a similar implementation study already underway in England and Northern Ireland,^24^ our study seeks to understand the organisational and other wide-ranging influences affecting the implementation of REACH-HF in Scotland, in order to inform potential large-scale roll-out of the intervention. A key factor shaping implementation is that a given intervention may not produce the same effects when transferred from one context to another and, crucially, from a randomised trial to the real world. Target population characteristics may differ in key ways, such as geographical location (urban/rural) or relative deprivation. Moreover, there may be significant contextual differences between sites and teams delivering a healthcare intervention, such as the size of the team or familiarity with a given approach. Such contextual differences may produce adaptations in what is delivered and how (ie, impacting fidelity to the intervention design). This may in turn shape intervention results—including any proven benefit—when compared with an RCT.^25^ Adaptability to context may also impact the sustainability of an intervention, that is, the extent to which it is embedded in everyday practice.^22^

We draw specifically from UK Medical Research Council (MRC) guidance on evaluation of complex interventions, particularly using process evaluation methodology.^26^ Process evaluation is an established means by which to understand implementation by assessing: fidelity (the degree to which the intervention was delivered as intended); context (barriers to and facilitators of implementation, including those that might explain variation in outcomes), and mechanisms of impact.^23^ As the mechanisms by which the REACH-HF intervention changes behaviour have been described and explored elsewhere,^12 13^ we focus here on fidelity and context in the new delivery setting. Integration of process and outcome data can generate better understanding of, for example, whether and how adaptations to implementation, or differences among sites, explains any observed variation in outcomes, as well as informing improvements for future roll-out.

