We will assess patient outcomes before and after administering the 12-week programme with 35 people with HF (140 total). Members of the HF team at each site will be interviewed. Detailed information of the costs and utilisation of the provision of the REACH-HF programme will be collected. Given the ongoing COVID-19 crisis, the start of data collection for the study has been delayed, but will begin in November 2020. NHS Greater Glasgow and Clyde will act as study sponsor.

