### The intervention

REACH-HF is a home-based, health professional-facilitated, 12-week CR programme supporting self-care in patients with HF. Three health professionals with CR and/or HF experience from each Beacon Site will attend a 2 days online REACH-HF training course facilitated by the Heart Manual Department, NHS Lothian (formerly a 3 days face-to-face training delivered in Edinburgh, the course has been adapted to accommodate current restrictions). Training focuses on the seven steps of successful facilitation of REACH-HF (in turn based on a person-centred care approach): (1) build rapport; (2) assess needs and build understanding of HF; (3) support self-management and progress monitoring; (4) discuss exercise and well-being; (5) summarise and plan next steps; (6) review progress; (7) support long-term maintenance. As such, training includes sessions on psychology, behaviour change, physical activity, engaging caregivers and newly adapted components to address intervention delivery during the COVID-19 pandemic. Following training, facilitators are then asked to implement REACH-HF. The programme—described in detail elsewhere^11 12^—is outlined in box 1.

Box 1The Rehabilitation EnAblement in CHronic Heart Failure (REACH-HF) Intervention*The Heart Failure Manual*, which provides information about HF for the person with HF, to increase understanding of the condition and address common misconceptions.Information on and strategies for managing HF, and further relevant advice on, for example, managing lifestyle risk, managing depression and anxiety, and getting support from others.A choice of two exercise training programmes: a chair-based programme (via DVD and online) and a walking programme; with a recommendation that these should be engaged in three times weekly, alongside general physical activity.A stress-management programme, with relaxation techniques (provided in the manual and in audio format) to help cope with anxiety and depression.A progress tracker designed to facilitate an individual’s learning from experience through self-monitoring of behaviour and symptoms. (this prompts help seeking as appropriate).A *Family and Friends Resource* to increase caregiver understanding of HF, to enable them to support the person with HF’s self-care and well-being.Face-to-face and telephone facilitation over 12 weeks by a health professional trained to deliver the REACH-HF programme.

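### The sample size makes no allowance for clustering and the stated analysis mentions neither facilitator nor site, although the study means to ask whether site differences explain outcomes

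*Protocol article*

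**What the plan says.** **Sample size** (Data analysis). The text reads "We require 130 participants to detect" a pre-post MLHFQ change of at least 5 points. The inputs follow: "This calculation is based on a MLHFQ SD of 24 points", a within-patient "correlation (r=0.72"), and attrition of at most 10%. No power, ICC or design effect is given. Study design sets recruitment at four sites, "with 35 people with HF (140 total").

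**Analysis** (Data analysis, CR participant-related outcomes). The primary analysis is a within-patient comparison in completers at 4 months: "All within-patient outcome comparisons will be presented as mean difference with 95% CI". Neither facilitator nor site appears.

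**Delivery** (The intervention). "Three health professionals with CR and/or HF experience from each Beacon Site will attend a 2 days online REACH-HF training course". With four sites this gives 12 trained facilitators.

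**Use of site differences.** The Introduction expects sites and teams to differ in ways that may shape results. It says that integrating process and outcome data can help show whether and how adaptations, or "differences among sites, explains any observed variation in outcomes". Under Fidelity, "Fidelity checklist scores will be collated at facilitator, site and total sample levels". The Context analysis section then places fidelity, context and participant outcomes in one matrix and looks for synergies that indicate the key findings. The Discussion says the findings will inform larger-scale roll-out.

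**The concern.** Patients who share a facilitator or a site may change by similar amounts. The protocol expects such differences, but its sample size allows for none and its stated analysis does not mention them. Two separate things are at stake.

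- **Precision of the pooled change.** Roll-out would involve other facilitators. For that inference, variation between facilitators belongs in the standard error, and an interval that leaves it out overstates precision if the variation exists.
- **Interpretation of site differences.** Outcomes are to be read beside fidelity and context. The article describes no interval for a site-level outcome and no check on whether sites differ by more than chance. With about 31 completers per site, gaps that look clinically important can arise from sampling error alone and then attract a contextual explanation.

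**Working it through.** **Inputs from the protocol article:** SD 24; r = 0.72; target change 5 points; attrition 10%; 35 patients at each of 4 sites; 3 trained professionals per site.

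**Assumptions:** two-sided 5% (matching the 95% CI); facilitator ICC of change 0 to 0.05; equal caseloads; one facilitator per patient.

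**1. Reproducing the 130.**
- SD of change = 24 × √(2 × (1 − 0.72)) = 17.96.
- n = ((1.96 + z_power) × 17.96 / 5)², divided by 0.90 for attrition.
- 80% power: 102, then 113. 85% power: 116, then 129 (132 with a t reference). 90% power: 136, then 151.
- Of these, only 85% power fits the 130, and that power is not stated. The design effect in this calculation is 1, so patients are taken as independent.

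**2. Facilitator clustering.**
- Completers: 140 × 0.90 = 126. Per facilitator: m = 126 / 12 = 10.5.
- Design effect DE = 1 + (m − 1) × ICC = 1 + 9.5 × ICC.
- True half-width = 1.96 × 17.96 × √(DE / 126).
- Coverage of the unadjusted interval = 2Φ(1.96 / √DE) − 1.
- Power at 5 points uses the normal approximation with the clustered standard error.

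| Facilitator ICC (assumed) | DE | True half-width | Coverage of unadjusted 95% CI | Power at 5 points |
|---|---|---|---|---|
| 0 | 1.00 | 3.14 | 95% | 88% |
| 0.02 | 1.19 | 3.42 | 93% | 82% |
| 0.05 | 1.48 | 3.81 | 89% | 73% |

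The required widening is √DE: none, 9% and 21%. With 12 clusters, a t reference on 11 df gives half-widths of 3.52, 3.84 and 4.28.

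**3. Site gaps under pure chance.**
- Completers per site: 126 / 4 = 31.5. SE of a site mean = 17.96 / √31.5 = 3.20.
- 95% half-width of one site mean: about 6.5 points (t reference; 6.3 with 1.96).
- 95% half-width of a two-site difference: about 9.0 points (t reference; 8.9 with 1.96).
- Simulating four site means with the same true effect and no clustering, the best-to-worst gap averages 6.6 points and exceeds 5 points in about 69% of studies.
- With 117 completers (130 × 0.90) the figures are 6.8 points and 71%.

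**The case against.** - **The article does not commit to an unadjusted analysis.** A mean difference with a 95% CI is a reporting format that a clustered analysis also meets, and the statistical analysis plan is not shown. This stands. Independence is demonstrated for the sample size only; for the analysis, the text is silent.
- **A reader might infer that the interval is too narrow as a matter of fact.** The documents do not support that. It requires an ICC above 0, which they do not give, and inference beyond these facilitators. At ICC 0 nothing changes. If these sites and facilitators are the whole target, their variation does not make the pooled interval too narrow. The roll-out aim favours the wider inference but does not supply an ICC.
- **A reader might infer that site differences will be mostly chance, or that the study will explain noise.** Neither is shown. The Introduction asks whether and how differences matter, and the Context analysis section names no site contrast. The 6.6-point figure shows what chance alone can produce, not what share of an observed gap is chance. With 29.25 completers per site (117 / 4), chance makes up 63% of the between-site variance at a site ICC of 0.02 but only 39% at 0.05.
- **The two parts may seem to conflict, since one needs clustering and the other assumes none.** They are separate conditional statements. Facilitator variation without any true site effect also makes site means noisier: at a facilitator ICC of 0.05 with three facilitators per site, the site-mean SE rises to 3.89 and the expected gap to 8.0 points.
- **Few clusters limit any remedy.** This stands. Variance estimates from 12 facilitators or four sites will be imprecise. A test of site heterogeneity has only about 19% power at a site ICC of 0.02 and 39% at 0.05, so it cannot serve as a gate.

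**Conclusion.** The point holds in conditional form. The 130 is an independent-patients calculation, and the described analysis mentions neither facilitator nor site, although delivery is clustered and the protocol expects that to matter.

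The loss of precision is modest over the range shown: for generalisation to other facilitators, the interval should be 0% to 21% wider for ICCs of 0 to 0.05. This rests on an assumed ICC, equal caseloads and one facilitator per patient.

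The site-level part is firmer because it needs no ICC. It rests only on the protocol's SD, correlation, attrition and recruitment per site. Gaps of 5 to 7 points between the best and worst site are ordinary even when all sites share the same true effect, so site outcomes should not enter the matrix without their uncertainty.

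**What to change.** 1. Keep the pooled paired mean change as the main estimate.
2. Add a sensitivity analysis of MLHFQ change with a facilitator random intercept and small-sample degrees of freedom. Enter site as either fixed or random, not both; a fixed site effect gives no site variance and no shrunken site estimates. Say that variance estimates from 12 facilitators will be imprecise.
3. Report each site's change with its 95% CI, and a heterogeneity estimate with its uncertainty, before site outcomes enter the integrative matrix. Treat site contrasts as exploratory, and note that gaps of 5 to 7 points are expected by chance.
4. State that the 130 assumes independent patients, and show precision over a range of ICCs that includes 0.

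**Cost.** A somewhat wider interval in the sensitivity analysis and a little more analysis work. Sites are known, and the Facilitator Log kept for each participant should allow patients to be linked to facilitators, so no new data collection should be needed.
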